### Endpoints and assessments

2.3

The co-primary endpoints are dose reductions due to toxicity and PFS, defined as the time from randomisation until the date of either objective radiological disease progression or combined biochemical and clinical progression or death. The reasons for dose reductions will be recorded. Objective radiological disease progression will be assessed according to the Response Evaluation Criteria in Solid Tumours (RECIST) version 1.1, or modified RECIST according to the Gynecologic Cancer Intergroup (GCIG) if there is no measurable disease at baseline [22,23]. Biochemical progression is assessed according to the GCIG criteria for CA-125 and clinical progression will be established by the treating physician [23].

For toxicity, adverse events will be scored according to the Common Terminology Criteria for Adverse Events (CTCAE) version 5.0 [24]. Patient health status and quality of life will be measured with the EuroQol 5 dimensions 5 levels questionnaire (EQ-5D-5L) version 1.1 [25]. Patient satisfaction in terms of cancer therapy will be assessed with the Cancer Therapy Satisfaction Questionnaire (CTSQ) [26]. To measure costs from the societal perspective for the cost-effectiveness analysis, the Institute for Medical Technology Assessment (iMTA) Productivity Cost Questionnaire (iPCQ) and iMTA Medical Consumption Questionnaire (iMCQ) will be used [27,28]. ctDNA levels in plasma will be measured with shallow Whole Genome Sequencing (sWGS) and/or a hybrid-capture based Next Generation Sequencing (NGS) panel, dependent on the most recent insights at time of analysis. ctDNA levels will be corrected for germline and clonal haematopoietic variants with matched peripheral blood mononuclear cells. Olaparib plasma concentrations will be measured by cross-validated liquid chromatography tandem mass-spectrometry assays [21,29,30]. Intratumoral olaparib concentrations will be assessed from optional tumour biopsies. The frequency of the above-mentioned assessments is outlined in Table 2.

**Table 2 tbl2:** Overview of measurements in PROACTIVE-B study.

	Baseline	Week 4	Week 6	Week 8	Week 12	Every 3 months	Every 6 months	At progression
Clinical evaluation	X	X		X	X	X	X	
Laboratory	X	X		X	X	X	X	
Adverse events	X	X		X	X			
Radiological evaluation	X				X		X	
ctDNA	X	X		X	X			X
Plasma olaparib PK		X		X	X			
Intratumoral olaparib PK				X				X

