### Sample size calculation

2.6

Separate sample size calculations were performed for the two primary endpoints tolerability and efficacy. The type I error of 0.05 was distributed between both outcomes.

For non-inferiority of tolerability, the non-inferiority margin for dose reductions due to toxicity was set at 24 %. With a type I error of 0.01, power of 80 %, and an incidence of dose reductions of 28 % in each group [31], 71 patients need to be randomised to each treatment group. The non-inferiority margin for tolerability of 24 % is relatively large. This has been extensively discussed with the clinicians and patient advocates experienced in the treatment with olaparib. The most prominent adverse events related to olaparib therapy are anaemia and gastro-intestinal symptoms [35]. Since patients who start olaparib are initially closely monitored, these adverse events are usually detected shortly after start of olaparib and are easily and effectively managed with dose reductions. Therefore, the clinical impact of these side effects is acceptable, and the larger non-inferiority margin of 24 % was accepted.

For non-inferiority of efficacy, the non-inferiority margin for PFS rate at twelve months was set at 15 %. With a type I error of 0.04, power of 80 %, and an estimated PFS at twelve months of 88 % in each group, 64 patients need to be randomised to each treatment group [31]. The non-inferiority margin for efficacy of 15 % was set according to the EMA guideline [36]. The margin demonstrates superiority to placebo as olaparib increased progression-free survival at 12 months by 33 % compared to placebo [31]. Moreover, the non-inferiority margin has been discussed and endorsed by clinicians and patient advocates.

Thus, the total sample size was set at 142 patients, of which 128 will receive olaparib for high-grade, BRCA-mutated ovarian cancer after response on first-line platinum-based chemotherapy.

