### Statistical analysis

2.7

An intention-to-treat, and per protocol, analysis will be performed in line with guidelines. The per-protocol analysis will be leading, but it is not expected that cross-over will take place. Proportions of patients with dose reductions due to toxicity at twelve months will be compared between both treatment arms with the Chi-square test for proportions. Additionally, a Kaplan-Meier approach will be used to compare PFS rates between both treatment arms in the efficacy population.

Linear mixed-effects models will be used to evaluate differences in patient health status and therapy satisfaction over time and between treatment arms. Descriptive statistics will be used to describe adverse events and intratumoral olaparib concentration. The association between ctDNA levels and clinical outcomes (PFS/OS) will be explored with a Cox proportional hazard model with a correction for previously defined prognostic factors [37]. Additionally, cost-effectiveness will be analysed in line with the most recent guideline for economical evaluations in healthcare by the Dutch Healthcare Institute [38]. In line with this guideline, we will adopt a societal perspective and a life time horizon to calculate the costs per quality adjusted life year (QALY) in a cost-utility analysis [38].

The patterns and extend of missing data over time and between treatment arms will be explored. As the primary endpoints are easy to assess, missing data is expected to be minimal for the primary analysis. In case of unexpected high proportions of missing data or missing data that can be classified as Missing Not At Random (MNAR), imputation methods and/or sensitivity analyses will be applied [39].

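### The tolerability co-primary is tested with an unadjusted Chi-square test, which leaves baseline information unused and does not address the 24-point margin; a prespecified adjusted risk difference with a confidence limit is a cheap improvement

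*Protocol article*

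**What the plan says.** Section 2.7 (Statistical analysis) fixes the method for the tolerability co-primary: the twelve-month proportions with a dose reduction due to toxicity "will be compared between both treatment arms with the Chi-square test for proportions". No covariate or stratum is mentioned for this test.

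Section 2.6 (Sample size calculation) frames the same endpoint as non-inferiority: "the non-inferiority margin for dose reductions due to toxicity was set at 24" percent. The other inputs are "With a type I error of 0.01, power of 80" percent and "an incidence of dose reductions of 28 % in each group", from which "71 patients need to be randomised to each treatment group". The 0.01 is this endpoint's share of an overall error rate: "The type I error of 0.05 was distributed between both outcomes".

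Three other places bear on the choice of covariates:

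- Section 2.1 (Design) stratifies randomisation by tumour type and by response to chemotherapy.
- Section 2.6 states: "The most prominent adverse events related to olaparib therapy are anaemia and gastro-intestinal symptoms". It adds that such events are managed by lowering the dose.
- Table 2 in section 2.3, titled "Overview of measurements in PROACTIVE-B study", has a general laboratory row ticked at baseline. It does not list the individual tests.

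**The concern.** Two features of the named test stand out.

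First, it ignores baseline information that the trial will hold. The stratification factors are known for every randomised patient, and baseline laboratory tests are scheduled for all. If any of these predict dose reduction, an unadjusted interval for the risk difference is wider than it needs to be. With 71 per arm, chance imbalance in such a predictor also adds noise to the estimate. The article itself describes the 24-point margin as fairly wide, and its Discussion says it is uncertain whether boosting will raise adverse events. A tighter interval would therefore say more about tolerability at almost no cost.

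Second, an ordinary Chi-square test asks whether the two proportions are equal. Its p-value does not show whether an excess of 24 points has been excluded, which is the question the sample size was built on.

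**Working it through.** **Inputs from section 2.6:** dose-reduction rate 28% in each arm, margin 0.24, type I error 0.01, power 80%, 71 per arm. The article does not say whether 0.01 is one-sided or two-sided.

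**Step 1: reproduce the plan's figure.** With an unpooled variance and a one-sided 0.01,

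n per arm = 2 × 0.28 × 0.72 × (2.326 + 0.842)² / 0.24² = 70.25, rounded up to **71**.

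This matches the plan. Reading 0.01 as two-sided (0.005 per side) would need 82, so the one-sided reading is used below. At 71 per arm,

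SE = √(0.4032 / 71) = 0.0754, and power = Φ(0.24 / 0.0754 − 2.326) = **80.5%**.

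The unadjusted design meets its target.

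**Step 2: effect of adjustment.** If baseline covariates explain a share R² of the outcome variance, the variance of the risk difference is multiplied by about (1 − R²). The article gives no R², so a range including zero is assumed. The last column is 24 minus the half-width, with the SE held at its 28% value.

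| Assumed R² | SE (points) | Power at 71 per arm | One-sided 99% half-width (points) | Largest observed excess that still passes (points) |
|---|---|---|---|---|
| 0 | 7.54 | 80.5% | 17.53 | 6.47 |
| 0.02 | 7.46 | 81.4% | 17.35 | 6.65 |
| 0.05 | 7.35 | 82.7% | 17.09 | 6.91 |
| 0.10 | 7.15 | 84.9% | 16.63 | 7.37 |
| 0.20 | 6.74 | 89.2% | 15.68 | 8.32 |

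**Step 3: check by simulation.** There were 6,000 trials per setting, 71 per arm and 28% events. One standard normal covariate had an assumed odds ratio per SD. The unadjusted risk difference was compared with the standardised one.

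| Odds ratio per SD | Variance ratio | Power, unadjusted to adjusted |
|---|---|---|
| 1.5 | 0.98 | 80.8% to 81.7% |
| 2.0 | 0.92 | 80.4% to 83.5% |
| 2.5 | 0.87 | 81.3% to 86.8% |

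A repeat run gave the same variance ratios and powers within about one point. In the first run, type I error at 28% versus 52% was 0.8–0.9% unadjusted and 0.9–1.1% adjusted.

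**Step 4: room for covariates.** Expected events are 0.28 × 142 ≈ 40. Arm, two binary stratification factors and one continuous covariate make four coefficients, or about 10 events each. The tumour-type factor is sparse: only 14 patients are planned for other indications, and 0.28 × 14 ≈ 4 events are expected among them.

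**Step 5: the equality test at the margin.** If the true rates were 28% and 52%, a two-sided Chi-square test at 0.01 with 71 per arm would be significant about 64% of the time. It would be non-significant the other 36%. A non-significant result therefore cannot stand in for exclusion of a 24-point excess.

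**The case against.** The strongest case against is that this is a preference. An unadjusted comparison of randomised proportions is valid, it agrees with the formula behind 71 per arm, and it delivers the planned power. Chance imbalance in an unstratified covariate is not bias, because the unadjusted standard error already allows for it. Covariate choice is commonly left to an analysis plan, which is not shown here. All of this stands. It limits the point to an improvement of a method that the article does name.

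The case for haemoglobin in particular is also weaker than a reader might infer. It is tempting to say that baseline haemoglobin is collected and that anaemia is a leading cause of dose reductions. The documents support neither statement. Haemoglobin is not named anywhere, and Table 2 has only a general laboratory row. Section 2.6 calls anaemia one of the most prominent adverse events and says such events are managed by dose reduction, but it gives no ranking of causes and no share due to anaemia. The endpoint also pools gastro-intestinal toxicity, for which the documents suggest no link with haemoglobin. The documented stratification factors are therefore the first candidates.

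The size is assumed throughout. With a weak predictor the gain is close to zero. In the simulation a small part of it may come from the adjusted test being slightly less conservative.

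What the objection does not answer is the mismatch between an equality test and a margin. That holds with or without covariates.

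**Conclusion.** The point holds as a modest improvement. The named test leaves baseline information unused and does not itself address the 24-point margin. Adjustment would add nothing for a null predictor and about 1 to 4 power points for R² of 0.02 to 0.10 (80.5% to 81.4–84.9%). Over that range the largest observed excess that still passes rises by less than one point (6.47 to 7.37). These figures assume a one-sided 0.01, 28% in both arms, 71 analysed per arm and an R² that the documents do not supply.

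Two stronger readings should be avoided. One is that the trial is underpowered or its analysis invalid for want of adjustment. The reproduced 71 per arm and 80.5% power contradict this. The other is that non-inferiority will be claimed from a non-significant Chi-square result. The article does not say so: its objective and sample size are stated in terms of non-inferiority, and section 2.7 simply does not connect the test to the margin.

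**What to change.** Prespecify the primary tolerability analysis, before outcome data are seen, as follows:

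- **Estimate:** a twelve-month risk difference standardised over all patients in the analysis population, from a logistic model with arm and the stratification factors as far as event numbers allow. Add continuous baseline haemoglobin if it is confirmed as part of the baseline laboratory panel. Standardisation keeps the result on the marginal risk-difference scale, so the 24-point margin keeps its meaning.
- **Precision:** a robust or bootstrap standard error.
- **Decision rule:** tolerability is non-inferior if the one-sided 99% upper confidence limit lies below 24 points. State explicitly that the 0.01 is one-sided.
- **Sensitivity analysis:** the unadjusted risk difference with its confidence limit.

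The cost is a sentence or two in the plan and a little analysis work. No new data are needed if the baseline values are already recorded, and the sample size does not change. The downside is slight dependence on the model, which the unadjusted sensitivity analysis covers.

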### Design

2.1

PROACTIVE-B is a Dutch nationwide, open-label, randomised, multicentre trial comparing boosted olaparib therapy with standard dose olaparib monotherapy in patients with solid tumours (Fig. 1). Patients will be randomised 1:1 between standard olaparib monotherapy and the boosted therapy of olaparib and cobicistat by a variable block randomisation. Randomisation will be stratified by tumour type (BRCA-mutated, high-grade, serous ovarian cancer treated with olaparib after first-line platinum-based chemotherapy, or other) and response to chemotherapy (i.e., complete, or partial response). The standard full dose of olaparib monotherapy consists of 300 mg BID. The boosted full dose of olaparib consists of 100 mg BID with cobicistat 150 mg BID. Dose reductions will be performed according to Table 1, in line with the drug label and the physician's discretion. Patients will visit the outpatient clinic at baseline, after 4, 8, 12 weeks and thereafter every three months until progression or the end of olaparib therapy, in line with standard clinical care. Patients will continue treatment until they do not longer experience clinical benefit or until the end of treatment according to the drug label and/or treatment guideline. This current protocol is approved by the Medical Research Ethics Committee Oost-Nederland and is conducted in accordance with Good Clinical Practice and the Declaration of Helsinki.

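### Randomisation is stratified by response to chemotherapy, but the primary analyses named do not use that factor and so forgo a little precision if response is prognostic

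*Protocol article*

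**What the plan says.** Section 2.1 (Design) of the protocol article states that "Randomisation will be stratified by tumour type" and, as a second factor, by complete or partial response to chemotherapy. Allocation is 1:1.

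Section 2.7 (Statistical analysis) names the primary methods. Proportions with a toxicity-related dose reduction at twelve months "will be compared between both treatment arms with the Chi-square test for proportions". For efficacy, "a Kaplan-Meier approach will be used to compare PFS rates between both treatment arms in the efficacy population". No stratum or covariate is attached to either. The same section does announce a correction for known prognostic factors in the Cox model for ctDNA.

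Section 2.6 (Sample size calculation) sizes the two comparisons separately:
- Tolerability: the margin is 24 percentage points. "With a type I error of 0.01, power of 80 %, and an incidence of dose reductions of 28 % in each group", the result is that "71 patients need to be randomised to each treatment group".
- Efficacy: the margin is 15 points on 12-month PFS, with a type I error of 0.04, 80% power and 88% PFS in each arm, giving 64 per arm.

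Section 2.4 (Study population) defines the efficacy population as the 128 ovarian cancer patients. It pools the other 14 patients with them for tolerability, on the premise that dose-reduction incidence is similar across tumour types.

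**The concern.** Balancing the arms on a prognostic factor removes the between-stratum variation from the true sampling error of the treatment difference. A standard error that ignores the factor leaves that variation in, so the interval comes out slightly wider than it need be. The error is in the safe direction: false claims of non-inferiority do not become more likely, but a true one becomes slightly harder to show.

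Precision is scarce here. At 88% PFS, only 0.12 × 64 = 7.7, or about 8, PFS events per arm are expected by month 12. The stratum is recorded at randomisation, so using it needs no new data. In addition, the per-protocol analysis leads and early withdrawals may be replaced, up to about 30%. Both can disturb the balance that randomisation created, and a stratum-weighted estimate would guard against that for response.

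**Working it through.** **1. The plan's own figures.** The unstratified formula with a true difference of zero is n per arm = 2p(1−p)(z₁₋α + z₀.₈)² / margin².
- Tolerability: 2 × 0.28 × 0.72 × (2.326 + 0.842)² / 0.24² = 70.25, so 71.
- Efficacy: 2 × 0.88 × 0.12 × (1.751 + 0.842)² / 0.15² = 63.1, so 64.

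Both match when the stated type I errors are read as one-sided; two-sided readings give 82 and 79. Power at 71 and 64 per arm is 80.5% each. The plan therefore relies on no gain from stratification.

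**2. Which factor can matter.** The efficacy population is a single tumour stratum, so tumour type is constant there. For tolerability, the 14 other patients are 14/142 = 9.9% of the total, and the article assumes their dose-reduction rate is similar. Response to chemotherapy is the factor left.

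**3. Gain from stratifying (large-sample).** Let s be the share of partial responders and d the difference in rates between response strata. The stratified variance is (1 − r) times the unstratified one, with r = s(1−s)d² / [p(1−p)]. SE₀ is the unstratified standard error and SE₁ = SE₀√(1−r) the true one. Then:
- power of the unstratified analysis = Φ((margin − z·SE₀)/SE₁);
- power of the stratified analysis = Φ(margin/SE₁ − z).

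Example with s = 0.2 and PFS of 92% v 72%: r = 0.2 × 0.8 × 0.04 / 0.1056 = 0.0606, SE₀ = 0.0574 and SE₁ = 0.0557. Unstratified power is 81.3% and stratified power 82.7%.

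The article gives neither s nor d, so the values below are assumptions.

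| Partial share | 12-month PFS, complete v partial | Interval narrows by | Power, unstratified → stratified |
|---|---|---|---|
| 20% | 88% v 88% | 0 | 80.5% → 80.5% |
| 20% | 90% v 80% | 0.8% | 80.7% → 81.1% |
| 20% | 92% v 72% | 3.1% | 81.3% → 82.7% |
| 30% | 94% v 74% | 4.1% | 81.5% → 83.4% |

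More extreme inputs give more: with 40% partial responders and a 25-point gap, 82.4% → 85.7%.

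Tolerability, same formulas, p = 0.28, 71 per arm, one-sided 0.01:
- response, 20% share: 80.6% → 80.8% at a 10-point gap and 80.9% → 81.9% at 20 points (gains of 0.3 and 1.0 point);
- tumour type: no gain on the article's premise, and 80.7% → 81.2% even at a 20-point gap.

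**4. Error rate at the margin, efficacy.** Simulation with 64 per arm, fixed strata, complete follow-up, a 15-point deficit in each stratum and 400,000 runs per scenario, for the last three rows of the table:
- unstratified Wald: 4.2%, 4.0%, 3.9%;
- simple stratified Wald: 4.5%, 4.6%, 4.6%, against a nominal 4%.

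The cause of the excess is sparse data: about 13 to 19 partial responders per arm with roughly 3 to 5 events. Simulated power was 80.5% → 81.4%, 81.0% → 83.4% and 81.3% → 84.2%, but part of that gain comes from the raised error.

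**5. Score-type interval.** Same three scenarios, 1,000,000 runs. The test statistic is (D + 0.15)/√(Σw²V), where D is the stratum-weighted difference, w the stratum share and V the Miettinen-Nurminen variance restricted to a 15-point deficit. The error was 3.9% in all three and power 77.9%, 78.5% and 78.7%. The unstratified score test had errors of 3.8%, 3.6% and 3.5% and power of 77.8%, 78.2% and 78.7%. The level is held, but the like-for-like gain in power shrinks to 0 to 0.3 points.

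**The case against.** The strongest objection is that the article is silent on strata, not committed to ignoring them. It condenses a fuller protocol, and a statistical analysis plan may add the factor. That stands as a caution. Two things weigh against treating it as mere omission: the Chi-square test for proportions is an unstratified test, and the same section states prognostic adjustment where it is intended, for ctDNA.

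A reader might also infer stronger things that the document does not support:
- **Power is lost against the plan.** It is not; 71 and 64 per arm give 80.5% without stratification.
- **The unstratified efficacy test runs well below its level, at about 3.4 to 3.7%.** That comes from a large-sample formula with 88% in both arms. Simulated at the margin, the error is about 3.9 to 4.3%, close to nominal.
- **Both factors and both endpoints suffer.** Tumour type is constant for efficacy and assumed irrelevant for tolerability.
- **Response was chosen because it predicts PFS.** The article gives no reason for the choice and no rates by response.

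The objection that a simple stratified Wald interval would be worse on type I error than the method it replaces also stands, and it shapes the fix.

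**Conclusion.** The point holds as a minor one. Response to chemotherapy is used to randomise but not in the primary methods named. Those methods are valid and reach the planned power. What is forgone is about 0 to 2 points of efficacy power and 0 to 1 point for tolerability by large-sample calculation, and zero if response is not prognostic. The efficacy range assumes 20 to 30% partial responders and gaps of up to 20 points between strata; the tolerability range assumes a 20% share and the same gaps. None of these inputs is in the document. With an interval that holds its level at 64 per arm, the efficacy gain may sit at the bottom of the range. The case for the change then rests mainly on matching the analysis to the design and on protection against imbalance in response.

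**What to change.** State in the analysis plan that:
- the primary efficacy estimate is the difference in 12-month Kaplan-Meier PFS rates, weighted by response stratum;
- the tolerability estimate is a risk difference stratified by response, with the 14 other patients kept as one stratum and not split by response;
- the intervals use a score-type method (for example stratified Miettinen-Nurminen for dose reductions) or a small-sample-corrected variance (for the Kaplan-Meier difference), not a simple stratified Wald interval;
- sparse strata are merged by a rule fixed in advance;
- the unstratified results are reported as sensitivity analyses.

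Tumour type need not enter the efficacy analysis.

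The cost is wording only: no new data and no more patients. The downsides are the merging rule and care over the interval. The chosen method should be simulated for both level and power before it is fixed, since a score-type interval, stratified or not, had slightly under 80% power in the scenarios above.

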To ensure feasibility of the protocol, this study is aligned with the current standard clinical practice as much as possible. Additional follow-up visits outside the study protocol are accepted and monitored for adverse event reporting as well. Questionnaires will be sent out online to reduce burden for the clinic and research staff, but also to make it as convenient as possible for patients who can fill in the questionnaires at a moment that fits them best.

The wide inclusion criteria of the study will result in a study population that reflects the real-world population. This will lead to broad external validity of our results. Of note, there is no exclusion criterion for patients treated with comedication that are substrates for CYP3A. These drugs could also be affected by cobicistat and, therefore, patients are screened for drug-drug interactions through routine workflows. Relevant interactions may limit the use of cobicistat. Due to the extensive experience with these drugs in antiretroviral therapy, this is considered a manageable hurdle [40].

Besides the clinical evaluation of the boosted therapy, this study incorporates several emerging research topics. In the past years, ctDNA analysis have provided valuable insights in its clinical validity in several cancer types [41]. In patients with ovarian cancer, ctDNA is correlated with the volume of disease and holds promise as a biomarker for disease monitoring [42,43]. This is interesting, considering the poor concordance between CA-125 and radiological progression in patients treated with PARP-inhibitors [44]. Moreover, reversion mutations could be detected in ctDNA of patients after treatment with olaparib and cediranib, which could provide valuable insights for treatment optimization [45].

Also, tumour biopsies will shed light on the intratumoral olaparib concentration, which might be increased with the boosted therapy and could therefore be a potential tool to convert resistance. Preclinical studies have shown that tumours are able to express CYP3A as a detoxification mechanism [18,20]. By inhibiting CYP3A, PK boosting might even increase intratumoral olaparib concentrations by CYP3A-inhibition and could therefore improve efficacy. The tumour biopsies are optional in this study, but even a small number of biopsies will provide new insights.

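### The 12-month PFS co-primary is planned as an unadjusted Kaplan-Meier comparison; this is valid, but forgoes a small, nearly free gain in precision from baseline data already collected

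*Protocol article*

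**What the plan says.** Section 2.7 (Statistical analysis) describes the efficacy comparison in one sentence: "a Kaplan-Meier approach will be used to compare PFS rates between both treatment arms in the efficacy population". The words raw, crude and unadjusted do not appear, but no covariate or stratification factor is named either.

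Section 2.6 (Sample size calculation) gives the decision rule: "the non-inferiority margin for PFS rate at twelve months was set at 15" percent. It continues "With a type I error of 0.04, power of 80 %, and an estimated PFS at twelve months of 88 % in each group", and concludes that "64 patients need to be randomised to each treatment group".

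Section 2.1 (Design) sets the allocation: "Patients will be randomised 1:1 between standard olaparib monotherapy and the boosted therapy of olaparib and cobicistat by a variable block randomisation". The stratification factors are tumour type and complete or partial response to chemotherapy. In the efficacy population tumour type is constant, so response is the only randomisation factor that varies.

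The one model in section 2.7 with prognostic correction is the ctDNA analysis of PFS and OS, which "will be explored with a Cox proportional hazard model with a correction for previously defined prognostic factors". Table 2 schedules laboratory tests and ctDNA at baseline.

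**The concern.** Few events carry the efficacy verdict: 12% of 128 is about 15 by month 12, or about 8 per arm. With so few, some of the random variation in the estimated difference comes from how baseline prognosis happens to fall between the arms. Only response to chemotherapy is balanced by design. Adjusting for baseline prognosis removes part of that variation, and with a suitable method the estimand stays the marginal 12-month difference that the margin refers to.

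Two features make adjustment somewhat more useful here. The per-protocol analysis leads, and patients who withdraw within three months without an event may be replaced, up to about 30%. Both can loosen the balance that randomisation gives.

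What is at stake is a modest amount of power. The validity of the comparison is not in question.

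**Working it through.** **Inputs.** From section 2.6: 12-month PFS 88% in both arms (event risk 12%), margin 0.15, alpha 0.04, power 80%, n = 64 per arm. Prognostic strength of the covariates is an assumption, because the article gives none. Full 12-month follow-up is assumed, so that the Kaplan-Meier rate equals the proportion.

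**1. The plan's own figure.** n per arm = (z0.96 + z0.80)² × 2 × 0.88 × 0.12 / 0.15² = (1.7507 + 0.8416)² × 0.2112 / 0.0225 = 63.1, rounded up to 64. This matches. Reading 0.04 as two-sided gives 79, so the plan is one-sided 0.04 with an unadjusted variance.

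**2. Planned precision.** SE = √(2 × 0.88 × 0.12 / 64) = 0.0574. Power = Φ(0.15 / 0.0574 − 1.7507) = 80.5%.

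**3. Decision boundary at 8 control events.** Upper limit = difference + 1.7507 × SE.
- 8 vs 10: 0.0313 + 1.7507 × 0.0614 = 0.139, passes.
- 8 vs 11: 0.0469 + 1.7507 × 0.0627 = 0.157, fails.

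The tolerated excess is two patients (2/64 = 3.1 points). It is 3 for 4 to 6 control events, 2 for 7 to 10 and 1 for 11 to 13.

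**4. Gain by formula.** Adjustment multiplies the SE by √(1 − R²), where R² is the assumed share of outcome variance explained.

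| Assumed R² | SE factor | Power | n per arm for equal precision |
|---|---|---|---|
| 0 | 1.000 | 80.5% | 64 |
| 0.02 | 0.990 | 81.3% | 63 |
| 0.05 | 0.975 | 82.3% | 61 |
| 0.10 | 0.949 | 84.2% | 58 |
| 0.20 | 0.894 | 87.9% | 52 |

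For response to chemotherapy alone, with 10 to 50% partial responders and an odds ratio of 1.5 to 5 (both assumed), R² is 0.002 to 0.07 and power 80.6 to 83.1%.

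**5. Gain by simulation.** Two normal baseline covariates with a combined log-odds SD of about 0.7 to 1.3 (assumed), linear adjustment of 12-month status, robust SE, 12,000 trials per setting. Across repeated runs:
- The ratio of adjusted to crude SD at equal true rates was 0.94 to 0.98.
- Power rose by about 1 to 4 points.
- Type I error at 12% vs 27% was 0.038 to 0.044 adjusted and 0.041 to 0.046 crude.
- Covariates with no prognostic value cost about 0.5 point of power.

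**6. Does it move the boundary?** At 8 vs 11 the room under the margin is 0.15 − 0.0469 = 0.1031 and the crude half-width is 0.1098. A pass needs an SE factor below 0.1031 / 0.1098 = 0.939, a reduction of just over 6%. With 5% the limit is 0.0469 + 0.95 × 0.1098 = 0.151; with 6% it is 0.0469 + 0.94 × 0.1098 = 0.1501. Both fail, the second only just.

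**The case against.** The strongest reply is that nothing here is wrong. An unadjusted comparison of randomised arms is valid and matches the sample size basis. The article is a condensed text, a Kaplan-Meier approach can be stratified or standardised, and covariate lists often sit in the analysis plan, which is not shown. Randomisation is already stratified by response to chemotherapy, which is related to disease burden. Most of this stands, and it limits the point to a recommendation. What remains is that the article names a method for a co-primary endpoint and sizes the trial on its unadjusted form, while a slightly more precise method is available with data already collected.

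Four stronger readings are tempting, and the article does not support them:
- *Section 2.7 is inconsistent, because it corrects for prognostic factors in the ctDNA model but not between arms.* The ctDNA analysis is a non-randomised association in which confounding has to be handled. The arm comparison is protected by randomisation.
- *Chance imbalance is an extra threat to the verdict.* Under the same assumptions, a 1-SD imbalance moves the crude difference by 1.1 to 1.7 points, but the crude standard error already contains that variation. Exact type I error of the crude test is 0.043.
- *Adjustment would rescue a result at the two-patient boundary.* On the arithmetic above, it would not within the assumed range.
- *Baseline ctDNA is the natural covariate, since "ctDNA is correlated with the volume of disease".* Section 2.3 leaves the assay open until the time of analysis, so a detectable/undetectable variable cannot be firmly defined now.

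Baseline CA-125 is also only presumed. It enters the PFS definition, but Table 2 lists laboratory tests without naming it.

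**Conclusion.** The point holds as a minor, optional improvement. The planned comparison is valid and its sample size is right. Adjusting for baseline prognosis would reduce the standard error by about 2 to 6% and raise power by about 1 to 4 points, with type I error still near 0.04.

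These figures rest on an assumed combined log-odds SD of 0.7 to 1.3. They come from two normal covariates and fully observed 12-month status, so they approximate a pseudo-value analysis and do not test it directly. The simulation had no stratification factor. The boundary calculation uses the planned event rate.

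**What to change.** Make the primary efficacy estimate a covariate-adjusted marginal difference in 12-month PFS. Either regress 12-month Kaplan-Meier pseudo-values on arm and covariates with identity link and robust standard error, or standardise predictions from a model. Compare the one-sided 0.04 confidence limit with the 15-point margin.

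Adjust for response to chemotherapy and at most one further baseline prognostic variable that is named in advance and recorded for all patients, for example log CA-125 if it is in the baseline laboratory panel. The cap reflects the roughly 15 expected events. Leave ctDNA out unless its assay and cut-off are fixed beforehand. Fix the variables before outcome data are examined, and keep the unadjusted Kaplan-Meier difference as supportive.

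The cost is a change of analysis wording and a check of what the baseline laboratory panel contains. It needs no new visits or patients. The statistical price if the chosen covariates prove uninformative is about 0.5 point of power.
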